**Fig. 1 Fig1:**
[figure not shown]
Conceptual framework

HOLA is a multi-component, health promotion intervention designed to prevent depression and anxiety in at-risk elderly Latinos. This prevention approach will be tested against a *fotonovela*, an enhanced psychoeducation control condition in a sample of Latino elderly with minor or subthreshold depression or anxiety. As described below, HOLA builds on prior work research [27] using physical activity to treat major depression in older adults.

#### Intervention description: content and structure of HOLA

The first component of HOLA is a social and physical activation session. Prior to beginning the group exercise phase, each participant will meet individually with a CHW for the physical and social activation session. This session will last 30 minutes. The purpose of this session is to (a) educate potential participants about the goals of the intervention; (b) motivate participants to engage in physical activity; (c) increase participants’ social activities; (d) identify potential obstacles that may interfere with meeting the demands of the intervention; and (e) brainstorm ways to overcome these obstacles. Participants will meet individually with the CHW for 30 minutes after week 8 to discuss progress of physical and social activity goals.

The second component is a moderately intense, group walk, led by a CHW for 45 minutes, three times a week, for 16 weeks. Moderate intensity is defined as a rating between 11 and 13 on the Borg Scale of Perceived Exertion [41]. Walks will be conducted with a group of six participants. Each walk will begin with 10 minutes of stretching and warm up. Then, participants will walk for 30 minutes. The walk will conclude with 5 minutes of stretching and cool down. Blumenthal and colleagues [27] showed that this intensity and amount of physical exercise is associated with greater remission of major depression in older adults. It is hypothesized that this amount and frequency will also be effective in the prevention of major depression and anxiety disorders in older Latinos with subthreshold symptoms. The groups will be mixed gender and will include bilingual and monolingual Spanish-speaking participants.

The third component consists of scheduling pleasant events. During the cool down phase of each walking session, the CHW will ask each participant to identify a pleasant event that they intend to do with another person before the next meeting. Individuals may choose to do this activity with another member of the group, with family, or with friends outside the group. The CHW will be trained to problem solve (for example, brainstorm) if a member of the group cannot think of a pleasant event. Subsequent sessions will start with participants reporting on how effectively they implemented their pleasant event plan while the CHW and the group provide positive reinforcement and feedback. This component provides a means to generalize the intervention into the participants’ everyday lives and relationships.

Mood ratings will be taken directly before and after each walk so participants can see, in real time, changes in their moods. A pedometer will be given to each participant prior to the first group walk, and will be used to track each participant’s progress and provide motivation. The group exercise will be carried out at a centrally located park that is owned and operated by the Miami-Dade County Parks and Recreation Department and is open to the public.

#### Comparison condition: content and structure of enhanced psychoeducation through *fotonovela*

The *fotonovela* was chosen as a control condition over usual care because it is a health-related intervention in its own right and relevant to older mentally ill Latinos who may have low literacy [42]. *Fotonovelas* are booklets that use posed photographs and simple text bubbles to portray soap opera stories that convey educational messages. *Fotonovelas* differ from common educational materials in that they incorporate popular images, cultural norms, simple text, dramatic stories, and vivid pictures to raise awareness, promote health, and combat stigma [42, 43]. The *fotonovela* has not been shown to be effective in increasing mental health service use, nor has it been used as mental health treatment or as a prevention tool [43]. It, however, will help patients become aware of their condition.

Participants randomized to the enhanced psychoeducation will be given a copy of the theoretically informed and empirically grounded *fotonovela* developed by Cabassa and colleagues [44]. In addition, participants in the control condition will meet one month after they are given the *fotonovela* for an open forum to express opinions concerning the *fotonovela* as well as knowledge gained from reading the material. The PI, who is a clinical psychologist, will lead these discussion groups, which will consist of six control participants per group and last for an hour.

### Measures and analysis

#### Feasibility objective: recruitment, randomization, retention, and acceptability

As a pilot study, the randomized prevention trial will examine feasibility. Consistent with recommendations from biostatistical workgroups funded by NIH [45], this pilot study is not powered to test a hypothesis. Successful recruitment will be defined as meeting 100 % of targeted randomization (n = 60), with 20 % or less of eligible subjects refusing randomization. Randomization will be deemed adequate if the randomization scheme produces equal numbers of participants randomized to each condition. Adequate retention will be defined as 85 % or more of randomized subjects completing the post-intervention assessment. Acceptability is defined as 80 % or more of sessions attended by subjects. Data will also be collected on the proposed outcome measures to be tested in a definitive randomized controlled trial.

Study measures will be administered at baseline, end of intervention, and at 6 and 12 months post intervention. Eligible participants will be paid $25 upon completion of assessments at baseline, the end of the intervention, at 6, and at 12 months post intervention for a total of $100. Trained research assistants (RA) will administer all of the assessments and will be kept blind to randomized study assignment.

After the baseline assessment, participants will be randomly assigned to the HOLA intervention or to the *fotonovela* condition. Randomization will be carried out using an automated program embodying the strategies of permuted block randomization.

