### Participants

The pilot study will randomly assign 60 older (60+) Latino participants with minor or subthreshold depression or anxiety to the HOLA intervention (n = 30) or enhanced psychoeducation (n = 30). The sample size is sufficient to provide meaningful data on the feasibility and the other outcome measures of interest. Additionally, this sample size is consistent with other pilot studies of physical activity interventions [38, 39]. Informed consent will be obtained from each participant. For a detailed description of the inclusion/exclusion criteria, see Table 1.

**Table 1 Tab1:** Inclusion/exclusion criteria

Inclusion criteria	Exclusion criteria
• Self-identify as Latino; • Age 60+; • Have minor depression as defined by a primary DSM-IV Axis I diagnosis of minor depressive disorder or subthreshold depression defined as a score ≥ 3 on the Patient Health Questionnaire (PHQ-2), OR subthreshold anxiety as defined as a score ≥ 3 on the Generalized Anxiety Disorder-2 scale (GAD-2); • Absent of episodes of major depression and anxiety disorders for past 12 months; • Volunteer informed consent; • Have medical clearance for participation in an exercise program by a physician, physician’s assistant, or nurse practitioner; • Agree not to use antidepressant medication (since these subjects could have a partially treated episode of major depression or anxiety and thus would be inappropriate for a prevention trial); • Expect to stay in Miami for the next 12 months	• Currently residing in a nursing or group home; • Have a terminal physical illness expected to result in their death within one year; • Have a diagnosis of dementia, comorbid diagnosis of dementia, or significant cognitive impairment; • Presence of any Axis I psychiatric disorder or substance abuse during preceding 12 months; • History of psychiatric disorders other than non-psychotic unipolar major depression or anxiety disorder; • High suicide risk; intent or plan to attempt suicide in the near future; • Taking cognitive enhancing medication or psychotropic medications (e.g., antidepressants); • Unable to complete 10-meter walk test in less than 23 seconds average; • Heart rate exceeds 170 beats per minute OR systolic blood pressure exceeds 180 during 10-meter walk test; • Chest or leg pain, dyspnea, dizziness, feeling faint, or other significant symptoms while completing 10-meter walk test; • Have contraindications to exercise outlined in the American College of Sports Medicine standards.

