### Recruitment

A community-based recruitment strategy employing locations that older Latinos are likely to frequent (such as churches, laundromats, libraries, and hair salons) will be used. It is the mission of the Community Engagement Group to help facilitate links between researchers at UM and the community. The recruitment efforts will be led by the CHW, who will work with the community advisory board and the study team to devise recruitment strategies that are most appropriate. To the extent possible these would be informed by already successful attempts in this community. Examples include targeting high-volume areas (such as laundromats, hair salons, and flea markets) and using ads in the local Latino press (such as the newspaper and radio). In addition, local housing authorities, senior centers, and community health centers will be informed of the study and provided with promotional materials. The Miami-Dade County Parks and Recreation Department puts on regularly scheduled health fairs in which residents are provided with free health screens. The principal investigator (PI) and CHWs will be present at these events to ensure that every older adult who comes in for a health screening will be screened for depression and anxiety. At the same time, the UM Public Relations (PR) department will be informed and notified of the ongoing research. The PR department will be provided with the promotional materials for the study. UM sites such as those that make regular postings and newsletters will also be contacted and provided with an approved ad or communication regarding the project. The ad will also be posted in non-UM newsletters and advertisement sections.

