### Trial status

Study recruitment, assessment, and intervention delivery activities are ongoing at the time of submission.

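### Equal arm sizes cannot show that randomisation was adequate, because permuted blocks produce them by construction

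*Protocol article*

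**What the plan says.** The relevant text is in the protocol article, Methods, under the feasibility objective, which names randomisation in its heading beside recruitment, retention and acceptability. Each has its own success rule. For randomisation the rule is: "Randomization will be deemed adequate if the randomization scheme produces equal numbers of participants randomized to each condition".

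The end of the same section says how participants are assigned, once baseline assessment is done: by "an automated program embodying the strategies of permuted block randomization". No block size, choice between fixed and varying blocks, or stratification is given. An article commonly leaves these to the full protocol, and their absence is not part of this point.

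The Participants section plans for 60 people to be assigned "to the HOLA intervention (n = 30) or enhanced psychoeducation (n = 30"), a 1:1 allocation.

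Three other parts of the article bear on the point:

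- Recruitment succeeds on two joint conditions: "meeting 100 % of targeted randomization (n = 60), with 20 % or less of eligible subjects refusing randomization".
- Retention needs at least 85% of those randomised to complete the post-intervention assessment, and acceptability needs at least 80% of sessions attended.
- The Analysis section separately compares the arms at baseline with chi-square and t-tests.

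**The concern.** A feasibility criterion is useful only if it can fail for a reason connected with what it judges. Here the outcome being judged, equal numbers, is what the chosen method is built to deliver. The count of participants randomised to each arm is fixed by the block scheme. It does not move if an allocation becomes known too early, if two participants receive each other's assignment, or if someone declines the assigned condition after allocation, since that person still counts as randomised to it.

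At stake is the verdict that the pilot will hand to the definitive trial. A randomisation with any of these problems could be reported as adequate. Conversely, a well-run one could be reported as inadequate because recruitment ended partway through a block.

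**Working it through.** **Inputs.** N = 60 and 30 per arm (Participants section); permuted blocks and the equal-numbers rule (feasibility section). Block sizes are not in the article, so those below are assumptions covering a plausible range, without stratification.

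**The plan's own figure.** 30 + 30 = 60, which is consistent. The size rests on other pilot studies and not on a power calculation, so there is no formula to reproduce.

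**1. Fixed blocks that divide 60.** For sizes 2, 4, 6, 10, 12 and 20 every block is complete at 60 and each holds equal numbers per arm. P(30:30) = 1.

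**2. Fixed blocks that do not divide 60.** All complete blocks are balanced, so only the cut last block matters. If r places of a block of size b are used, the chance of an even split is C(b/2, r/2)² / C(b, r).

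- Size 8: 60 = 7 × 8 + 4, so r = 4. P = C(4,2)² / C(8,4) = 36/70 = 0.514. The largest difference is 4 (32 v 28).
- Size 16: 60 = 3 × 16 + 12, so r = 12. P = C(8,6)² / C(16,12) = 784/1820 = 0.431. The largest difference is again 4.

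**3. Randomly varying blocks** (simulation, 20,000 runs each, sizes equally likely):

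| Assumed sizes | P(30:30) | Largest difference |
|---|---|---|
| 2, 4 | 0.89 | 2 |
| 4, 6 | 0.78 | 2 |
| 2, 4, 6 | 0.81 | 2 |
| 4, 6, 8 | 0.72 | 4 |

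**4. Benchmark: simple randomisation, run correctly.** P(30:30) = C(60,30) / 2^60 = 0.103, so a sound procedure would miss the rule with probability 1 − 0.103 = 0.897.

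**Reading.** Across these cases the chance of passing runs from 0.103 to 1. It depends only on the method, the block size and where enrolment stops. Quality of conduct enters none of the formulas.

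**5. The neighbouring recruitment criterion, for contrast.** With 60 randomised, the refusal limit allows at most 60 / (1 − 0.20) = 75 eligible people, that is 15 refusals. Assuming recruitment continues until 60 accept, P(pass) is the binomial probability of at least 60 acceptances among 75:

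| True refusal rate | P(pass) |
|---|---|
| 10% | 0.997 |
| 15% | 0.911 |
| 20% | 0.569 |
| 25% | 0.195 |
| 30% | 0.035 |

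This criterion responds to what it is meant to measure. The equal-numbers rule does not.

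**The case against.** The strongest reply is that little hangs on this rule. The abstract lists recruitment, adherence, retention and acceptability as the primary outcomes, and randomisation adequacy is not among them. Someone who refuses the assigned arm and leaves counts against retention. Someone who stays but does not attend counts against acceptability. The baseline comparison looks at whether the groups are alike. Assignment is automated and follows baseline, and assessors are blinded. Equality is also not strictly guaranteed.

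Much of this stands, and it limits the consequence. It does not rescue the rule. The other criteria catch part of the harm under other names, and none of them feeds the randomisation verdict. Retention also leaves room: 0.85 × 60 = 51 completers are enough, so up to 9 losses still pass. The cases where equality fails are those in which the last block is cut, which says nothing about conduct.

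Two stronger readings are tempting, and the article does not support them:

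- A reader might infer that the recruitment criterion is equally empty because the target of 60 carries no time limit. The same sentence sets the 20% refusal limit, which is a real test. An accrual window may also stand in the full protocol.
- A reader might infer that allocations are predictable, since the community health worker leads both recruitment and the HOLA walks, and the principal investigator attends recruitment events and leads the control discussion groups. Guessing the end of a block needs knowledge of the block size and of the running order of allocations. The article does not say that either person has these.

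**Conclusion.** The concern holds for the randomisation criterion alone. Under the stated method, equal numbers are certain at 60 when all blocks are complete. Otherwise they are missed only because the last block is incomplete, with a difference of at most 4 participants under the block sizes examined. Stratification could leave several incomplete blocks and widen that difference, but the reading would be the same.

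The conclusion rests on the 1:1 plan, N = 60 and permuted blocks, all stated in the article. It does not depend on any particular block size. The consequence is modest: one declared feasibility verdict carries almost no information and could be favourable after a poorly run randomisation. No effect estimate and no primary feasibility outcome changes. It should still be corrected, because it is a stated decision rule that cannot measure what it judges, and correcting it is cheap.

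**What to change.** Replace the equal-numbers rule with a process criterion that can fail, in two parts:

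- No allocation is made or disclosed out of sequence, or before that participant's baseline assessment is complete. The article already places randomisation after baseline, so this makes a stated procedure checkable, for example against the randomisation program's log.
- At least a prespecified share of randomised participants accept and start their assigned condition. The investigators should set the threshold and define what counts as starting in each arm. As an example only, 90% would mean 0.90 × 60 = 54 of 60.

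Report arm sizes descriptively, with no pass mark. Participants randomised per month could be reported beside the target of 60; this is optional and would help in planning the definitive trial.

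The cost is a change of wording and one more feasibility count. The verdict may turn out less favourable than one based on equal numbers. Since the Trial status section says recruitment was already under way, the change should be dated and recorded as an amendment, with the threshold fixed before data on uptake of the assigned condition are reviewed.

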#### Screening

A two-step screening process will be used to identify potential participants (Fig. 2). The first step includes the PHQ-2 [46] to screen for depression, and the GAD-2 [47] scale to screen for anxiety. The Mini Mental Status Exam (MMSE) [48] will be used to screen for dementia. Potential participants must confirm safe participation by not having an acute or severe medical illness. A letter will be sent to the subject’s primary care physician describing the study and inquiring about any conditions prohibiting participation. The second step includes screening for psychiatric diagnosis with the Mini International Neuropsychiatric Inventory (MINI) [49]. The 10-meter walk test will be used to evaluate walking ability. It has demonstrated excellent reliability when used in older adults and shows comparable results as other, longer measures [50].

**Fig. 2 Fig2:**
[figure not shown]
Flow chart of screening and assessment

#### Study measures

In the full-scale trial the primary outcomes of this study will be the preemption of new and recurrent major depressive and anxiety disorders, as measured by the MINI [49], and change in depressive and anxiety symptom severity, as measured by the Quick Inventory of Depressive Symptoms, self-report (QIDS-SR) [51] and the Beck Anxiety Inventory (BAI) [52]. Both depression and anxiety episodes will be tracked because of their frequent co-existence as common mental disorders [53], and previous prevention trials have tracked both common mental disorders [54, 55]. Secondary outcomes of the full-scale study will include change in physical functioning, social engagement, and sedentary behaviors as measured by the WHO Disability Assessment Schedule (WHODAS 2.0) [56]; change in self-efficacy as determined with the General Self-Efficacy Scale [57]; and change in sleep quality using the Pittsburgh Sleep Quality Index (PSQI) [58].

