#### Analysis

Univariate analyses will be conducted to determine if randomization yielded equivalent groups by comparing demographics, background factors, key outcome variables and important covariates and potential moderators at baseline using chi-square and *t*-tests. Confidence intervals will be examined for differences between group means for all measures as a means of summarizing these analyses. If systematic differences between the two groups are found, propensity score matching will be used in statistical tests of outcomes. As a preliminary evaluation of the interventions, effect sizes will be calculated to assess for evidence of potential effectiveness. However, we accept that the study will not be powered to provide strong evidence against the null hypothesis. An intent-to-treat analysis will be conducted for the outcomes of interest, comparing the participants who were randomized to HOLA with those in the *fotonovela* condition. These analyses permit the strongest inferences to be drawn regarding the effects of physical activity and enhanced psychoeducation, but as previously discussed they may be underpowered. For a more conservative assessment, an as-treated analysis will be conducted, comparing participants randomized to and completing HOLA to those randomized to the *fotonovela*. These analyses may provide a more sensitive measure of the true effect of HOLA on reducing depression and anxiety symptom severity.

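### Continuous outcomes are worded as change, and the only adjustment stated depends on observed imbalance; adjusting every comparison for the instrument's own baseline score would narrow the intervals at no cost

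*Protocol article*

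**What the plan says.** All references are to the protocol article.

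- **Outcome wording (Study measures).** Symptom severity is given as "change in depressive and anxiety symptom severity, as measured by the Quick Inventory of Depressive Symptoms, self-report (QIDS-SR" together with the BAI. The next group follows the same pattern: "Secondary outcomes of the full-scale study will include change in physical functioning, social engagement, and sedentary behaviors" on the WHODAS 2.0, then change in self-efficacy and in PSQI sleep quality.
- **Which trial (Study measures).** The sentence on primary outcomes opens "In the full-scale trial the primary outcomes of this study will be the preemption of new and recurrent major depressive and anxiety disorders", so these definitions are attached to the later trial.
- **Use in the pilot (Feasibility objective).** "Data will also be collected on the proposed outcome measures to be tested in a definitive randomized controlled trial". The schedule is "Study measures will be administered at baseline, end of intervention, and at 6 and 12 months post intervention", so each instrument's baseline score will be in hand.
- **Analysis.** As a preliminary evaluation, "effect sizes will be calculated to assess for evidence of potential effectiveness", and the arms are compared by intention to treat. No estimator or model is named for the outcomes. Baseline characteristics are tested between arms. Matching on a propensity score enters the outcome tests only if those comparisons show systematic differences. No other adjustment is mentioned.

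**The concern.** The stated use of baseline data is a two-step rule: look for imbalance, and adjust only if it is found. When none is found, the text leaves a comparison of change between arms with no baseline covariate. Adjusting for an outcome's own baseline score is useful for a different reason. It removes predictable variation between participants, and so narrows the interval, however well balanced the arms happen to be. Tying adjustment to observed imbalance therefore gives up precision in the ordinary case.

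What is at stake is modest but real. The pilot lists potential effectiveness among its aims, judges it through effect sizes, and concedes that it is underpowered. Those effect sizes would be less precise than the same 60 participants allow. The residual SD and the baseline to follow-up correlation, which are useful for planning a baseline-adjusted definitive trial, are not among the quantities the article says it will report.

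**Working it through.** The article states no SD, effect size, power or interval width, so there is no figure of its own to reproduce.

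**Inputs from the article**
- Allocation: "to the HOLA intervention (n = 30) or enhanced psychoeducation (n = 30" (Participants), so n = 30 per arm.
- Retention threshold: "Adequate retention will be defined as 85 % or more of randomized subjects completing the post-intervention assessment" (Feasibility objective). 0.85 × 30 = 25.5, taken as 26 per arm.

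**Assumptions**
- Equal SD at baseline and follow-up; all widths below are in units of that SD.
- Baseline to follow-up correlation r is not given, so it is shown from 0.3 to 0.9.

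**Formulas**
- Variance of unadjusted change: 2·SD²·(1 − r).
- Residual variance of follow-up given baseline: SD²·(1 − r²) = SD²·(1 − r)(1 + r).
- Ratio, adjusted to change: (1 + r)/2, which is below 1 for every r < 1. It is 0.65, 0.75, 0.85, 0.90 and 0.95 at r = 0.3, 0.5, 0.7, 0.8 and 0.9.
- 95% half-width: t × √(variance × 2/n), with 2n − 2 degrees of freedom for change and 2n − 3 for the adjusted analysis. The adjusted variance is also multiplied by 1 + 1/(2n − 4) to allow for estimating the slope; at n = 30 this is 1 + 1/56 = 1.018.

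**Example, n = 30 and r = 0.5.** √(2/30) = 0.258 and t is about 2.00.
- Change: 2.00 × 0.258 × √1.00 = 0.517.
- Adjusted: 2.00 × 0.258 × √(0.75 × 1.018) = 0.452.
- Ratio: 0.517/0.452 = 1.14.

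**Results (95% half-width in SD units; percentages from unrounded values)**

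| r | Change, n = 30 | Adjusted, n = 30 | Change wider by | Change, n = 26 | Adjusted, n = 26 |
|---|---|---|---|---|---|
| 0.3 | 0.612 | 0.498 | 23% | 0.659 | 0.537 |
| 0.5 | 0.517 | 0.452 | 14% | 0.557 | 0.488 |
| 0.7 | 0.400 | 0.373 | 7.5% | 0.432 | 0.402 |
| 0.8 | 0.327 | 0.313 | 4% | 0.352 | 0.338 |
| 0.9 | 0.231 | 0.227 | 2% | 0.249 | 0.245 |

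Loss to follow-up at the retention threshold widens both intervals but leaves the relative penalty almost unchanged.

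**Does the word change cause the loss?** Write the adjusted model as Y = a + d·arm + b·B + e, where B is the baseline score. Subtracting B from both sides gives Y − B = a + d·arm + (b − 1)·B + e. The arm effect d and the residual e are the same, so the standard error is too. A simulated data set of 60 agreed: the arm effect was 0.0706 with SE 0.1886 for both outcomes. The loss arises only when B is left out of the model.

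**The case against.** The strongest reply is that the article nowhere says change will be compared unadjusted. It names what is measured, not how it is modelled, and a covariate list is normally left to an analysis plan or full protocol, neither of which is shown. This stands as far as it goes: silence on a covariate would not be a finding. But the article is not silent on baseline adjustment. It states a rule, and that rule makes adjustment depend on observed imbalance. The point rests on the rule.

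Three stronger readings are tempting, and the documents do not support them.

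- **That the outcome definition is itself defective because subtracting baseline adds noise.** The identity above shows otherwise: with the covariate in the model, change and follow-up score give the same answer.
- **That the definitive trial will be oversized.** Inverting the variance ratio gives 1/0.65 = 1.54 at r = 0.3 and 1/0.85 = 1.18 at r = 0.7, which might be read as 54% to 18% too many participants. Nothing in the article says that an SD of unadjusted change from this pilot will size the later trial.
- **That the correlation must be only moderate because entry can rest on a two-item screen.** Entry can also be through a diagnosis of minor depressive disorder, and the screening scales are not the outcome scales. At r of 0.8 or more the gain is small.

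It is also true that the change wording belongs to the full-scale trial and that no pilot success criterion depends on these scales. That limits the weight of the point. It does not remove it, because the pilot collects the same measures and computes effect sizes.

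**Conclusion.** The point holds in a limited form. The article words its continuous outcomes as change, collects the baseline score, and states no baseline adjustment other than matching triggered by imbalance. If change is compared without the baseline covariate, intervals would be about 7.5% to 23% wider than necessary for r from 0.7 down to 0.3, and 2% to 4% wider for r of 0.9 to 0.8. These sizes assume equal SDs and a correlation that the documents do not give; the direction holds for any r below 1 under equal SDs, apart from the small cost of estimating one slope. This is a cost-free improvement in precision, not an error that biases the comparison or threatens the pilot's feasibility conclusions.

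**What to change.** In the Analysis section, state that each continuous outcome (QIDS-SR, BAI, WHODAS 2.0, General Self-Efficacy Scale, PSQI) is compared between arms as randomized, with that instrument's own baseline score as a covariate for every participant, whether or not baseline imbalance is observed. The outcomes may stay worded as change. Report the adjusted difference with its 95% interval, and add the residual SD and the baseline to follow-up correlation for planning the definitive trial.

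The cost is a sentence or two of analysis wording. No new data, visits or participants are needed, and the feasibility outcomes and their thresholds stay as they are.
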